### Statistical analysis

#### Primary outcomes

FOBT participation will be compared between arms using a Chi-squared test. The change in coefficient method using log binomial generalized linear models (GLM) will then be used to check for potential covariates (for example, PHM factors, decisional conflict, gender, SES, age band, Internet access characteristics and so on) and to provide a final adjusted comparison of screening uptake rates. Change in decision stage will be analysed using analysis of covariance based on PAPM scores to compare the decision stage after the intervention having adjusted for the baseline stage.

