Participants in each of the two PDS arms will be required to access the PDS web site and log in with a unique user name and ID provided by the researchers. Once logged on, participants in both arms will complete a Baseline Survey (BS) that will collect demographic data, PAPM decision stage and measure PHM variables. Participants in the *Tailored PDS *arm will receive appropriately motivating or reinforcing messages tailored to their responses to the BS variables. In addition they will be able to access an electronic version of the NBCSP's consumer information booklet [26]. This provides information about the NBCSP, including information on bowel cancer, screening, and completing the FOBT kit. In the *non-tailored PDS *arm, participants will not receive any tailored messages upon completion of the BS but they will be able to access the NBCSP consumer information booklet. In the *paper-based *usual practice arm, the BS only (without an accompanying consumer information booklet) will be offered by mail. At that stage, all participants will be informed that they will receive an FOBT kit approximately 2 weeks after completion of the BS. This information will equate to the 'pre-notification' process employed in the NBCSP.

All participants who have not opted out of the trial at the BS phase and have completed a BS will receive a commonly used FOBT kit of the immunochemical type (Faecal Immunochemical Test, FIT) that does not require dietary or drug restrictions, and an invitation to screen. In the usual practice arm, the offer will consist of a mailed, personalised (by name and address) invitation to screen and will include printed educational material in the form of the NBCSP consumer information booklet. The offer to PDS participants will parallel that of the usual practice arm, with the distinction that the printed educational material will not be provided but both groups will be reminded that they may return to the PDS using their supplied username and password to re-visit messages (tailored arm) and the electronic version of the NBCSP consumer information booklet. A reminder will be sent 6 weeks after despatch of FOBT to those who have not returned their kit.

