Participants will be contacted by letter 1-2 weeks after receipt of their completed FOBT, or 12 weeks following the invitation to screen for those who haven't returned their kit during this period, and requested to complete an Endpoint Survey (ES) either by returning to the online site (PDS arms) or completing the accompanying ES in paper format (usual practice arm). The ES will re-measure the PHM/PAPM variables included in the BS and collect additional information relating to the outcome measures (Table 2).

**Table 2 T2:** Data collection stages

**Phase 1 Eligibility Questionnaire, self-completed on paper. Reminder sent 2 weeks after initial mailing**.
Questions addressing the inclusion and exclusion criteria (Additional file 1)
**Phase 2.1 Baseline Survey, self-completed on line or on paper as allocated. Reminder sent 2 weeks after initial mailing**.
Demographic characteristics
Age, sex, education, country of birth, marital status, employment status
PAPM stage
Decision stage for screening assessed by PAPM stage (never heard of FOBT, aware but not engaged, decided not to act, undecided, decided to act)
PHM constructs
Scores assessed on salience and coherence, cancer worries, response efficacy, social influence, perceived susceptibility [18]
Self efficacy
Score assessed on confidence to use an FOBT at home
Faecal aversion
Score assessed on distaste or embarrassment toward handling of faeces

**Phase 2.2 Invitation to screen, including FOBT. Sent 2-4 weeks after completion of baseline survey with reminder sent 6 weeks after initial invitation**.
Receipt or non-receipt of completed FOBT recorded by the Bowel Health Service (BHS), Repatriation General Hospital
Return of kit
Date of return of kit
Number of participants who contact the 'help line' provided as part of the standard BHS protocol

**Phase 3.1 Endpoint Survey, self-completed on line or on paper as allocated. Administered 1-2 weeks following receipt of completed FOBT, or 12 weeks following invitation to screen. Reminder sent 2 weeks after initial mailing**.
PAPM stage
PHM construct scores
Self efficacy score
Faecal aversion score
Participation in any other bowel cancer screening activity since entry into trial
Familial history of bowel cancer
Usefulness of the educational material
Satisfaction with content and ease of navigation (PDS arms)
Decisional satisfaction and conflict. Scores assessed by the Decisional Conflict scale [32]

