#### Participant outcome measures

The primary outcomes are (1) return of completed FOBT within 6 weeks (prior to reminder) and 12 weeks (after reminder); and (2) change in decision stage on the PAPM between intention expressed in the BS and decision stage as measured in the ES. Key secondary outcomes are (1) change in participant responses to the PHM variables between completion of the BS and the ES; (2) decisional conflict and satisfaction scores; and (3) satisfaction with the screening process. These and other measures are summarised by collection stage in Table 2.

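### Decisional conflict is listed as a candidate covariate for the adjusted comparison of FOBT uptake, although it is measured only after uptake is settled and is itself a secondary outcome

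*Protocol article*

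**What the plan says.** All references are to the Protocol article.

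- **Statistical analysis, Primary outcomes.** Uptake is first compared by a chi-squared test. Log binomial models, with covariates chosen by a change-in-coefficient rule, come next; their stated purpose is "to provide a final adjusted comparison of screening uptake rates". The candidates are given by example, in the words "check for potential covariates (for example, PHM factors, decisional conflict, gender, SES, age band, Internet access characteristics and so on". Nothing limits them to baseline values.
- **Study interventions, Baseline Survey.** Participants "complete a Baseline Survey (BS) that will collect demographic data, PAPM decision stage and measure PHM variables". Table 2 adds self efficacy and faecal aversion at that stage. Decisional conflict is not there.
- **Table 2, Phase 3.1 (Endpoint Survey).** This is the only place where the scale is collected: "Decisional satisfaction and conflict. Scores assessed by the Decisional Conflict scale [32". The survey is "Administered 1-2 weeks following receipt of completed FOBT, or 12 weeks following invitation to screen". The text agrees: "The ES will re-measure the PHM/PAPM variables included in the BS and collect additional information relating to the outcome measures".
- **Participant outcome measures.** The key secondary outcomes include "decisional conflict and satisfaction scores". The Secondary outcomes analysis compares these scores between arms.
- **Background, on decision aid format.** Tailored messages are expected to reduce decisional conflict.

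**The concern.** Covariate adjustment in a randomised comparison is safe for variables that neither the intervention nor the outcome can have changed. Decisional conflict fails on both counts here. It is scored after each person has returned a kit or let 12 weeks pass, so the act of screening can shape the answer. The trial's own rationale also expects tailoring to lower it.

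The selection rule adds to the risk. A change-in-coefficient rule keeps variables that move the arm coefficient. A score that depends on both arm and uptake does exactly that, and the rule cannot tell this apart from correcting a chance baseline imbalance.

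At stake is the adjusted estimate for the first primary outcome. Part of a real benefit of the tailored package could be adjusted away. The model could also use only people who completed the Endpoint Survey.

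**Working it through.** **1. The plan's own figures.** Sample size considerations gives 40% v 50%, 80% power, alpha 0.05 and 540 survey respondents per arm. The attrition step reproduces: 540 / (1 - 0.5) = 1080 per arm, and 3 x 1080 = 3240. The two-sided requirement is

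n = [1.960 x sqrt(2 x 0.45 x 0.55) + 0.842 x sqrt(0.24 + 0.25)]^2 / 0.10^2 = (1.379 + 0.589)^2 / 0.01, giving 388 per arm (408 with continuity correction).

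So 540 is more than the stated inputs need. Power at 540 is Phi[(0.10 x sqrt(540) - 1.379) / 0.70] = Phi(1.35) = 91.1%. The point below does not depend on this margin.

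**2. Order of events.** Randomisation, Baseline Survey, information, kit, uptake at 6 and 12 weeks, Endpoint Survey. Decisional conflict appears only at the last step. No baseline score exists, so the covariate list cannot be read as meaning one. The survey's timing also differs by outcome: 1-2 weeks after a kit is received, against 12 weeks after the invitation for non-returners.

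**3. What adjustment does.** Let A be arm, Y uptake and D the conflict score in SD units, with D = bA x A + bY x Y + e, where e is standard normal. The documents give neither bA nor bY; both are assumptions. By Bayes' rule,

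logit P(Y=1 | A, D) = logit P(Y=1 | A) + bY x (D - bA x A) - bY^2 / 2.

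The arm coefficient on the logit scale therefore changes from logit(0.5) - logit(0.4) = 0.405 to 0.405 - bA x bY.

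- At bA = -0.2 and bY = -0.5 it is 0.405 - 0.10 = 0.305.
- At bA = -0.4 and bY = -0.8 it is 0.405 - 0.32 = 0.085.
- If either effect is zero it does not move.
- If both effects lower conflict, the product is positive and the shift is toward the null. If returning a kit raised conflict, the shift would go the other way.

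**4. Risk ratio scale.** One simulated data set of 400,000 people, uptake 40% v 50%, with a log-link Poisson model standing in for the log binomial. The unadjusted risk ratio in these data was 1.243 (true value 0.50 / 0.40 = 1.25). Adjusted risk ratios:

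| Arm effect on conflict (SD) | Uptake effect 0 | -0.25 | -0.5 | -0.8 |
|---|---|---|---|---|
| 0 | 1.243 | 1.239 | 1.227 | 1.207 |
| -0.2 | 1.243 | 1.206 | 1.166 | 1.118 |
| -0.4 | 1.243 | 1.174 | 1.110 | 1.039 |

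**5. At the planned size.** A separate simulation used 600 trials per scenario, 540 per arm and robust standard errors, with an uptake effect of 0.5 SD. Unadjusted, the risk ratio was 1.25 with power about 91%. Adjusted, it was 1.18 with power 67% when tailoring lowers conflict by 0.2 SD, and 1.14 with power 49% at 0.3 SD. With no direct arm effect it stayed at 1.23 to 1.24.

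**6. Responders only.** A model containing an Endpoint Survey score drops everyone without that survey, unless values are imputed. The response rate is not in the readable text (Figure 1 is not shown). If response is unrelated to arm and uptake, the step 1 power formula gives:

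| Assumed response | n per arm | Power |
|---|---|---|
| 90% | 486 | 88.1% |
| 70% | 378 | 79.0% |
| 50% | 270 | 64.7% |

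**The case against.** The strongest reply is that decisional conflict is only an example of a potential covariate. The article commits to checking it, not to keeping it, and gives no threshold for the rule. That stands: the bias is conditional. A reader might infer that the adjusted effect is certain to be biased; the documents do not support that.

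Second, the chi-squared test comes first and uses no Endpoint Survey data. That also stands. It would be wrong to infer that the randomised comparison of uptake is compromised; an unbiased result sits beside the adjusted one. But the article gives the adjusted result the last word, so the point is not idle.

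Third, the sizes are assumed. The Background supports the direction of the arm effect, not its amount, and nothing says that returning a kit lowers conflict. With no uptake effect there is no bias. With no arm effect the change is small.

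Fourth, one might call the score a mediator. A score taken after uptake cannot mediate uptake. At most it stands in for conflict felt sooner, or reflects the decision already made. The objection rests on its timing, not on that label.

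Fifth, a reader might assume that Endpoint Survey response depends on having returned a kit. That is plausible, but the article does not say so.

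Finally, Baseline Survey variables are not perfectly clean either. They are collected after randomisation, online or on paper by arm, with 50% attrition expected. They do precede the intervention information and uptake, which is the distinction that matters here.

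**Conclusion.** The point holds in conditional form. The article names, as a candidate for adjusting a primary outcome, a variable that exists only after that outcome and that the trial elsewhere treats as an effect of the intervention. No reading of Table 2 makes it a baseline covariate. If it is retained and depends on both arm and uptake, the adjusted arm effect would be biased, probably toward the null, and confined to Endpoint Survey responders.

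Over the assumed range, a true risk ratio of about 1.25 becomes 1.24 at the mild end and 1.04 at the extreme, with 1.17 to 1.18 in the middle case. These figures show what could happen; they do not forecast this trial. PHM factors carry a similar risk, because they are measured at both surveys and the analysis section does not say which values enter the model. The chi-squared comparison and the sample size are unaffected.

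**What to change.** In Statistical analysis, Primary outcomes:

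- Delete decisional conflict from the covariates for FOBT participation.
- State that adjustment is allowed only for variables measured before the intervention information is shown, that is, from the Eligibility Questionnaire and the Baseline Survey.
- Specify PHM factors as Baseline Survey scores.
- Analyse decisional conflict only as a secondary outcome, or in a separately labelled exploratory analysis.

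With the candidates limited in this way, the change-in-coefficient rule can no longer pick a consequence of uptake. The cost is a sentence or two of text. No data collection, participants or sample size change, and the adjusted model no longer loses people for want of an Endpoint Survey.

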#### Secondary outcomes

Changes in participant responses to the PHM variables will be examined for their relationship to change in PAPM decision stage and FOBT participation. Log binomial GLMs will be used to determine the best joint predictors of participation. Scores on decisional conflict and satisfaction variables will be compared between the arms using a chi-squared test or Students t-test as appropriate. User satisfaction with the screening process will be assessed by qualitative research; the Framework analysis approach [27] will be utilised as it is suited to applied research that incorporates *a priori *issues and that intends to make recommendations for practice. Content analysis [28] will also be used to identify key themes and concepts.

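### Change in PHM scores is measured after FOBT participation is settled, so it cannot show what drove screening; the stated analysis of this outcome also does not compare the arms

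*Protocol article*

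**What the plan says.** Participant outcome measures in the Protocol article ranks PHM change first among the key secondary outcomes: "Key secondary outcomes are (1) change in participant responses to the PHM variables between completion of the BS and the ES".

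Statistical analysis, Secondary outcomes, gives its analysis: "Changes in participant responses to the PHM variables will be examined for their relationship to change in PAPM decision stage and FOBT participation". The following sentence is: "Log binomial GLMs will be used to determine the best joint predictors of participation". It lists no candidate variables and does not say at which survey they must be measured.

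Study interventions sets the timing of the ES: "Participants will be contacted by letter 1-2 weeks after receipt of their completed FOBT, or 12 weeks following the invitation to screen", the second date being for people who have not returned a kit by then. It adds: "The ES will re-measure the PHM/PAPM variables included in the BS". Table 2 gives the same schedule.

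Statistical analysis, Primary outcomes, names PHM factors (survey not specified) and decisional conflict among the possible covariates for the log binomial model of uptake. Table 2 lists decisional conflict at the ES only.

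For the other survey scores the Secondary outcomes paragraph does compare arms: "Scores on decisional conflict and satisfaction variables will be compared between the arms using a chi-squared test or Students t-test as appropriate". Decision stage on the Precaution Adoption Process Model (PAPM) is compared by analysis of covariance adjusted for baseline stage.

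**The concern.** A variable can explain participation only if it is fixed before participation. PHM change is not. Doing the test at home may itself alter confidence in it, worry or perceived susceptibility, so the association could run from participation to attitude. A participation model that admits PHM change would then present as drivers of screening some attitudes that are consequences of it. Such a result could steer the next round of tailored messages.

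Decisional conflict raises the same problem in the adjusted comparison of uptake, because it is measured after randomisation and after the outcome.

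Separately, the analysis stated for the first key secondary outcome makes no use of the randomisation. The Background describes tailored messages meant to reinforce or change PHM perceptions. A comparison of the randomised arms is the analysis that could show whether they do.

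**Working it through.** **Timing, by participant group**

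| Group | When participation is settled | When the second PHM score is requested |
|---|---|---|
| Returned within 12 weeks | at kit receipt | 1-2 weeks after receipt |
| Not returned by 12 weeks | at 12 weeks | 12 weeks after invitation |

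In neither group does the second score come before the outcome. The BS-to-ES interval also depends on the outcome. A kit received at week 3, for example, leads to an ES letter at week 3 + 1 to 3 + 2, that is week 4 to 5, against week 12 for a non-returner. The non-returner has also had the 6-week reminder before the ES.

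**Size, under stated assumptions**

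The documents give no figure for the effect of completing a kit on PHM scores, so there is no plan figure to reproduce.

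Inputs:
- n = 1620, from Sample size considerations (3240 × 0.5). This is the number offered a kit, so it is an upper limit for ES respondents. n = 1200 is an assumed lower value.
- Participation p = 0.45, assumed as the midpoint of the plan's 40% and 50%.
- PHM change has no influence on participation, and completing the kit shifts the later score by d within-group SD (assumed, varied).

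The expected test statistic is d × √(n p (1 − p)), and the chance of two-sided p < 0.05 is about Φ(statistic − 1.96).
- n = 1620: √(1620 × 0.45 × 0.55) = √400.95 = 20.02.
  - d = 0.1: 2.00 − 1.96 = 0.04, giving 52%.
  - d = 0.2: 4.00 − 1.96 = 2.04, giving 98%.
- n = 1200: √297 = 17.23.
  - d = 0.1: 1.72 − 1.96 = −0.24, giving 41%.
  - d = 0.2: 3.45 − 1.96 = 1.49, giving 93%.

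The relative risk of participation per SD of change is about exp(d(1 − p)): exp(0.055) = 1.06 for d = 0.1, and exp(0.11) = 1.12 for d = 0.2.

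Simulation (300 or 400 trials per setting; Poisson regression with robust standard errors in place of the log binomial model) agrees:

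| Shift d | Significant, n = 1620 | Significant, n = 1200 | RR per SD, n = 1620 |
|---|---|---|---|
| 0 | 4% | not run | 1.00 |
| 0.1 | 50-54% | 43% | 1.05 |
| 0.2 | 96-99% | 94% | 1.12 |
| 0.3 | 100% | not run | 1.18 |

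The first row shows that the model itself is sound. The excess comes entirely from the direction of the effect.

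**Is an arm comparison feasible?**

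Power for an assumed 0.2 SD difference between two arms is about Φ(0.2 × √(n/2) − 1.96):
- 540 per arm: 3.29 − 1.96 = 1.33, giving 91%.
- 432 per arm: 2.94 − 1.96 = 0.98, giving 84%.
- 270 per arm: 2.32 − 1.96 = 0.36, giving 64%.

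**How far could kit completion distort it?**

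If uptake differed by the planned 10 percentage points and completion shifted scores by 0.2 SD, the part of an arm difference due to completion alone would be 0.10 × 0.2 = 0.02 SD. This assumes that ES response does not depend on kit return.

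**The case against.** The strongest reply is that the article does not say PHM change will be a predictor. The first sentence speaks only of a relationship. The predictor sentence names no variables, and PHM and self-efficacy scores are also collected at the BS, so a model built on baseline scores fits the text. This stands: a reader might infer that the plan commits to predicting participation from PHM change, and it does not. What remains is that nothing excludes it. The two sentences are adjacent, and the naming of decisional conflict as a covariate for uptake shows that the plan admits at least one variable measured after the outcome.

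Second, a fuller plan may contain an arm comparison of PHM scores, and the abstract lists analysis of variance among its methods without tying it to an outcome. This also stands. It would be wrong to conclude that the trial leaves the effect of tailoring on attitudes untested. The supported statement is that the analysis the article gives for this outcome does not compare arms, while those for uptake, decision stage and decisional conflict do.

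Third, the percentages follow from an assumed shift. Agreed: they show that an association says nothing about direction, not how large the distortion would be here.

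Fourth, a reader might suppose that participants know their test result when they answer the ES. The article does not say when results are sent, and the argument does not need it.

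Finally, relating PHM change to PAPM change is not open to the same timing objection, since both are measured at the same two surveys.

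**Conclusion.** The timing point holds on the text. PHM change and decisional conflict are observed after participation, and when they are observed depends on participation. Neither can support a statement about what led people to screen, and neither belongs in a predictive or covariate-adjusted model of uptake. That the plan would in fact enter PHM change as a predictor is the natural reading, not a stated one.

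The arm-comparison point is weaker, because a fuller plan is not at hand. It rests on the contrast between this outcome and its neighbours in the same section.

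The size depends wholly on the assumed shift and on n. At n = 1620 the chance of a spurious significant association runs from about 4% with no shift to 50-54% at 0.1 SD and 96-99% at 0.2 SD. The unadjusted chi-squared comparison of uptake and the PAPM analysis of covariance are unaffected. The matter concerns a key secondary outcome and the covariates of the adjusted uptake model. It should be corrected, because the foreseeable error is a causal conclusion in the wrong direction and the correction is cheap.

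**What to change.** In Statistical analysis:
- Keep the analysis of PHM change against PAPM change.
- State that the log binomial predictor model uses only variables measured at or before the BS. Apply the same limit to the covariates of the adjusted uptake comparison, which removes decisional conflict and makes PHM factors mean BS scores.
- Report any association between PHM change and FOBT participation as descriptive. Note that the ES follows participation and that its timing depends on it.
- For the first key secondary outcome, add an analysis of covariance of ES PHM scores by arm with the BS score as covariate, in line with the PAPM analysis, for tailored PDS against each of the other two arms. Note that an arm difference may partly reflect having completed the kit. If a fuller plan already contains this comparison, refer to it.

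No new data are needed, since PHM scores are collected at both surveys. The cost is a few sentences, a small extra analysis and a more cautious reading of a secondary outcome.

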**Methods/design:**

A randomised parallel trial comprising three arms will be conducted. Men and women aged 50-74 years (*N *= 3240) will be recruited. They must have access to the Internet; have not had an FOBT within the previous 12 months, or sigmoidoscopy or colonoscopy within the previous 5 years; have had no clinical diagnosis of bowel cancer. Groups 1 and 2 (PDS arms) will access a website and complete a baseline survey measuring decision-to-screen stage, attitudes and cognitive concerns and will receive immediate feedback; Group 1 will receive information 'tailored' to their responses in the baseline survey and group 2 will received 'non-tailored' bowel cancer information. Respondents in both groups will subsequently receive an FOBT kit. Group 3 (usual practice arm) will complete a paper-based version of the baseline survey and respondents will subsequently receive 'non-tailored' paper-based bowel cancer information with accompanying FOBT kit. Following despatch of FOBTs, all respondents will be requested to complete an endpoint survey. Main outcome measures are (1) completion of FOBT and (2) change in decision-to-screen stage. Secondary outcomes include satisfaction with decision and change in attitudinal scores from baseline to endpoint. Analyses will be performed using Chi-square tests, analysis of variance and log binomial generalized linear models as appropriate.

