#### Randomisation

Those who have indicated, by return of the completed EQ, that they have read the study information, are eligible and willing to participate in the study will be randomly assigned to one of three arms (Figure 1). Block randomisation using random block size will be utilised, and stratification will be performed to ensure that the numbers of participants receiving each intervention are closely balanced within each Australian State.

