### Sample size considerations

Randomisation of 3240 participants (1080 in each arm) takes into consideration predicted attrition of 50% at BS survey phase, followed by screening offers being distributed to 1620 survey respondents (540 in each arm). This permits detection of differential FOBT uptake of at least 10% between two groups (e.g., 40% vs 50%) with 80% power and alpha of 0.05. To recruit this number of participants, an initial sample of 18,000 needs to be approached, given our estimated attrition rates throughout the study (Figure 1).

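### The t-test named for the decisional conflict and satisfaction scores compares two groups, but the trial has three arms and no pair is named

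*Protocol article*

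**What the plan says.** The abstract sets the design: "A randomised parallel trial comprising three arms will be conducted". The arms are tailored PDS, non-tailored PDS and paper-based usual practice.

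Participant outcome measures lists the decisional conflict and satisfaction scores among the key secondary outcomes. Table 2 places decisional satisfaction and conflict in the Endpoint Survey only, scored on the Decisional Conflict scale, so they have no baseline value. The same table has a separate item on satisfaction with content and navigation, which it marks as applying to the PDS arms.

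For these outcomes the statistical section states: "Scores on decisional conflict and satisfaction variables will be compared between the arms using a chi-squared test or Students t-test as appropriate". It names no pair of arms, no overall three-arm test and no covariate.

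Three other places bear on the point:

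- The abstract's summary of methods: "Analyses will be performed using Chi-square tests, analysis of variance and log binomial generalized linear models as appropriate". It mentions no t-test.
- The analysis of the second primary outcome: "Change in decision stage will be analysed using analysis of covariance based on PAPM scores", adjusted for baseline stage. This is the only method of the analysis-of-variance family in the body.
- The Randomisation section: "stratification will be performed to ensure that the numbers of participants receiving each intervention are closely balanced within each Australian State".

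**The concern.** A Student's t-test compares the means of two groups. The sentence applies it to a comparison between the arms of a three-arm trial. The closing qualifier in that sentence does not help, because it chooses between a chi-squared test and a t-test, and neither compares three means.

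An analyst who keeps to the wording has three options: test several pairs, pick one pair, or merge two arms. The first raises the false-positive rate unless something is added to control it. The other two leave the choice of comparison open until the data are in hand.

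The outcome is not incidental. The background argues that tailored messages should raise satisfaction with the decision and lower decisional conflict, and these scores are the direct test of that argument.

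**Working it through.** **The plan's own figure.** The protocol gives no standard deviation, target difference or power for these scores. Its only sample-size figure concerns FOBT uptake: 540 per arm for 40% vs 50%, "with 80% power and alpha of 0.05". The standard two-sided formula gives

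n = [1.96·√(2·0.45·0.55) + 0.842·√(0.40·0.60 + 0.50·0.50)]² / 0.10² ≈ 388 per arm.

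So 540 is more than the stated inputs need (power about 91%). The inflation for 50% attrition does reproduce: 540 / (1 − 0.5) = 1080 per arm, and 3 × 1080 = 3240. None of this bears on the choice of test for the scores.

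**Inputs for the check.**

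- Three arms of equal size (abstract; Sample size considerations).
- Alpha 0.05. It is stated for the uptake calculation; carrying it over to the scores, and taking it as two-sided, are assumptions.
- Large-sample normal behaviour of the test statistics. This is reasonable because 540 per arm are expected to pass the Baseline Survey, although fewer will complete the Endpoint Survey.

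**Step 1: what a t-test can do here.** Three arms give 3·2/2 = 3 pairs. For arms i and j with common standard deviation σ and n per arm, the statistic is Z_ij = (mean_i − mean_j) / (σ√(2/n)). One such statistic covers one pair, so comparing all three arms takes three of them. The stated hypothesis needs two: tailored vs non-tailored PDS, and tailored vs paper.

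**Step 2: false-positive rate when all arms are equal.** If the tests were independent, the chance of at least one result beyond ±1.96 would be:

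- three tests: 1 − 0.95³ = 0.143
- two tests: 1 − 0.95² = 0.0975

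Tests that share an arm are correlated, so the true values are lower. A simulation of 400,000 null trials with three equal arms gave:

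| Procedure, per score | Chance of at least one false positive |
|---|---|
| Three pairwise tests at 0.05 | 12.2% |
| Two tailored-arm contrasts at 0.05 | 9.0% |
| Three-arm F test at 0.05 | 5.0% |
| Pairwise tests only after a significant F test | 5.0% |
| Three pairwise tests at 0.05/3 | 4.4% |

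**Step 3: which outcomes are affected.**

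- A categorised score compared by chi-squared: not affected, since that test takes three arms.
- Satisfaction with content and navigation: not affected, since it is marked for the two PDS arms and a two-group t-test suits it.
- A continuous score collected in all three arms, of which decisional conflict is the clear case: affected.

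**Step 4: abstract against body.** The abstract lists chi-square tests, analysis of variance and log binomial models. The body names chi-squared tests, a t-test, analysis of covariance and log binomial models. The t-test is missing from the abstract, and plain analysis of variance is missing from the body.

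**The case against.** The strongest reply is that the sentence does not say the tests will be pairwise or unadjusted. A journal article may leave named contrasts and multiplicity for secondary outcomes to a fuller document, and such silence is no fault. That stands as far as it goes. A reader might infer that the plan commits to uncontrolled pairwise testing, and the text does not support that. The 12% and 9% describe what follows if the t-test is applied pair by pair with nothing added. The fault is narrower: the article names a specific test that cannot make the comparison it is given, and a later plan would have to overrule it rather than fill it in.

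Four further inferences are tempting and go too far.

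- *The abstract contradicts the body on these scores.* The abstract assigns analysis of variance to no outcome and may mean the analysis of covariance for decision stage. The two method lists do not match, but this is not a direct contradiction.
- *Every comparison in the sentence is faulty.* The chi-squared option and the PDS-only satisfaction item are sound.
- *Ignoring State and baseline stage is an error.* The protocol promises no such adjustment for these scores, and they have no baseline value. State stratification is there to balance numbers. Leaving these variables out costs some precision and causes no bias, and ignoring the strata is usually slightly conservative. The size of the loss cannot be given, because the documents do not say how much of the score variance these variables explain.
- *Across two scores the error is 23%.* That figure needs independent scores, which is implausible when Table 2 ties satisfaction and conflict to one scale. At an assumed correlation of 0.8 it is about 18%. The per-score figures need no such assumption.

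It is also fair to say that the hypothesis concerns tailored PDS against the other two arms. For that purpose 9% is the more relevant figure than 12%.

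**Conclusion.** The point holds in a limited form. For continuous scores measured in all three arms, the named t-test does not fit the design. Used pair by pair at 0.05 with no further control, it gives about a 12% chance of at least one false positive per score over all pairs, or 9% over the two tailored-arm contrasts. A three-arm F test gives 5%. These figures assume two-sided tests, equal arms, large samples and no true difference between arms.

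The mismatch between the abstract's list and the body should be cleared up, but it does not by itself show which test was meant for these scores. The effect is confined to a key secondary analysis. The FOBT comparison, the analysis of decision stage and the sample size are not touched.

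**What to change.** In the Secondary outcomes paragraph of the statistical analysis:

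1. For continuous scores measured in all arms, replace the t-test with one linear model per score. Include arm at three levels and State, the randomisation stratum. Baseline PAPM stage may be added as an option.
2. Report the overall arm test and the two contrasts that the hypothesis names: tailored vs non-tailored PDS, and tailored vs paper.
3. Keep the chi-squared test for categorised scores, and keep the two-group t-test only for items collected in the PDS arms alone.
4. Make the method list in the abstract agree with the body.

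The protocol already uses a model of this kind for decision stage, so no new method is brought in. State and baseline stage are already held, so no data collection changes and the cost is a few lines of wording.

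A formal adjustment of the two contrasts (Dunnett or Holm) is a matter of judgement for secondary outcomes: it gives tighter error control but wider intervals. Reading the contrasts only after a significant overall test already holds the error at 5% when all arms are equal. If just one pair of arms is equal, only one true null hypothesis remains, and it is tested at 0.05. Adding the full set of baseline PHM scores as covariates is optional.
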